# Effects of High and Low-To-Moderate Intensity Exercise During (Neo-) Adjuvant Chemotherapy on Muscle Cells, Cardiorespiratory Fitness, and Muscle Function in Women With Breast Cancer: Protocol for a Randomized Controlled Trial

**DOI:** 10.2196/40811

**Published:** 2022-11-11

**Keywords:** resistance training, endurance training, muscle strength, muscle endurance, anthracyclines, taxanes

## Abstract

**Background:**

(Neo-)adjuvant chemotherapy for breast cancer is effective but has deleterious side effects on muscle tissue, resulting in reduced skeletal muscle mass, muscle function, and cardiorespiratory fitness. Various exercise regimens during cancer treatment have been shown to counteract some of these side effects. However, no study has compared the effect of high-intensity training versus low-to-moderate intensity training on muscle tissue cellular outcomes and physical function in patients with breast cancer during chemotherapy.

**Objective:**

The aim of this substudy within the Physical Training in Cancer (Phys-Can) consortium is to evaluate and compare the effects of high and low-to-moderate intensity exercise on muscle cellular outcomes, muscle function, and cardiorespiratory fitness in women with breast cancer undergoing (neo-)adjuvant chemotherapy. We further aim to investigate if the effects of chemotherapy including taxanes on muscles will be different from those of taxane-free chemotherapy.

**Methods:**

Eighty women recently diagnosed with breast cancer scheduled to start (neo-)adjuvant chemotherapy will be randomized to a combination of strength and endurance training, either at high intensity or at low-to-moderate intensity. Testing of muscle function and cardiorespiratory fitness and collection of muscle biopsies from the vastus lateralis muscle will be performed before the first cycle of chemotherapy (or after 1 week, when not possible) (T0), halfway through chemotherapy (T1), and after completion of chemotherapy (T2). It is estimated that approximately 50% of the participants will be willing to undergo muscle biopsies. To separate the effect of the treatment itself, a usual care group with no supervised training will also be included, and in this group, testing and collection of muscle biopsies will be performed at T0 and T2 only.

**Results:**

This study is funded by Active Against Cancer (Aktiv mot kreft) (May 2013) and the Norwegian Cancer Society (December 2018). Inclusion started in December 2016 and the last participant is expected to be recruited in December 2022. As of June 2022, we enrolled 38 (19 with biopsies) participants to the high-intensity training group, 36 (19 with biopsies) participants to the low-to-moderate intensity training group, and 17 (16 with biopsies) participants to the usual care group. Data analyses will start in fall 2022. The first results are expected to be published in spring 2024.

**Conclusions:**

This study will generate new knowledge about the effects of different training intensities for women with breast cancer during chemotherapy treatment. It will give further insight into how chemotherapy affects the muscle tissue and how physical training at different intensities may counteract the treatment side effects in muscles. The results of this study will inform the development and refinement of exercise programs that are effective and compatible with the multidisciplinary management of breast cancer.

**Trial Registration:**

ClinicalTrials.gov NCT05218876; https://tinyurl.com/ysaj9dhm

**International Registered Report Identifier (IRRID):**

DERR1-10.2196/40811

## Introduction

Breast cancer is the most common type of cancer in women in Europe [1]. Advances in treatment and improved survival rates have led to an increased focus on addressing the persistent adverse effects of treatment, including cancer-related fatigue, reduced physical capacity, weight gain, and reduced quality of life [2]. A common (neo)adjuvant treatment for women with breast cancer is chemotherapy with anthracyclines or taxanes or a combination of both. Observational studies have shown an approximately 10% decrease in maximal oxygen uptake (VO_2max_) during chemotherapy [3]. This is concerning since low VO_2max_ has been associated with higher mortality among patients with breast cancer [4]. The reduced VO_2max_ might be related to the reported cardiotoxic effects of anthracyclines [5], but reductions in VO_2max_ are also reported without any signs of impaired cardiac function [6], suggesting there are other mechanisms contributing to the observed decline. Chemotherapy including anthracyclines has been reported to reduce muscle force-generation capacity and other essential muscle functions in both animal studies [7-9] and in patients with breast cancer [10]. Anthracyclines have also been demonstrated to reduce muscle fiber cross-sectional area (CSA) [8] and mitochondrial function [11] in rodents. These findings are supported by analysis on muscle biopsies from 2 small-scale studies on patients with breast cancer undergoing chemotherapy [12,13], which confirm the deleterious effects of chemotherapy on muscle size, mitochondrial structures, and muscle function. However, it is difficult to differentiate if these negative effects on the muscle are the direct effects of chemotherapy, the cancer itself, or indirectly from the reduced levels of physical activity, which is common in patients with cancer [14]. Regardless of cause, loss of skeletal muscle mass has been associated with reduced physical functioning and increased toxicity, that is, poor tolerance to chemotherapy and thus, worse prognosis [15,16].

Our clinical experience suggests that muscle function is more affected during taxane treatment than during anthracycline treatment. One frequent comment from patients during taxane treatment is the feeling of acidification during light and moderate physical activity. Taxanes have been reported to induce peripheral neuropathies [17], and one of the main mechanisms underlying the observed neuropathy is the deleterious effects on mitochondria [17,18]. A similar negative effect on the mitochondria in the skeletal muscle fits well with the abovementioned comments from patients. However, no studies have investigated if the muscular cellular effects of treatment including taxanes are different from those of treatment without taxanes and if including taxanes in the treatment leads to a different response to an exercise intervention. We will recruit patients receiving treatment with anthracyclines, taxanes, or a combination of both. If a sufficient number of patients is given each of the different treatments, we aim to investigate if the effects of treatment including taxanes on the muscle cells are different from those of taxane-free treatment on the muscle cells.

Strength training improves muscular strength and muscle size [19], and endurance training improves mitochondrial volume and mitochondrial function [20]. Therefore, physical training is a potential effective countermeasure to the chemotherapy-induced impairments in skeletal muscle mass and function. In women with breast cancer, physical training has been shown to reduce the loss of muscle strength and cardiorespiratory fitness commonly observed during treatment [2]. However, the physiological mechanisms underlying this protective effect are largely unknown.

Endurance training has been reported to reduce the cardiotoxic effects of anthracyclines in rodents [21-23]. The possible protective effects of physical training on skeletal muscles during chemotherapy for breast cancer have only been studied in 1 small-scale study. Mijwel and colleagues [12] showed that participating in a training program that combined high-intensity intervals to either strength training or aerobic exercise (moderate intensity) during treatment had beneficial effects on muscle fiber CSA and mitochondrial enzymes in the 2 intervention groups. Furthermore, these beneficial effects showed an inverse correlation with changes in cancer-related fatigue, indicating that the training effect on muscle fiber CSA and mitochondrial enzymes during chemotherapy might reduce cancer-related fatigue [12]. However, there is a need for studies including more participants to verify these findings and to investigate the physiological mechanisms underlying this protective effect. Regular exercise during treatment also seems to have several other beneficial effects on both treatment efficiency and reducing the other side effects of treatment [24,25]. Some of these effects seems to be related to increased production of antitumor myokines in the exercising muscles [26], and this aspect will also be investigated in the analyses of muscle biopsies in this study.

To date, most studies have compared a single exercise intervention to usual care or interventions with no physical activity. High-intensity training is shown to induce larger improvements in VO_2max_ and muscle strength in both healthy individuals and in various patient populations [27-29]. However, it is not known to which extent chemotherapy interferes with normal adaptation to physical training. A recent systematic review and meta-analysis reported that longer sessions and higher weekly volume and duration are associated with more beneficial changes in VO_2max_ after endurance training in various populations with cancer during (neo)adjuvant treatment [30]. However, the effects of different training intensities were unclear.

Data from the main study under the Physical Training in Cancer (Phys-Can) consortium showed that combined strength and endurance training with both low-to-moderate intensity and high intensity was feasible in patients with different types of cancer. Furthermore, high-intensity training led to better effects on muscle strength and VO_2max_ compared to low-to-moderate intensity training [29]. However, muscle biopsies were not included in the main study; therefore, how training with different intensities affect muscular cellular outcomes is not known. Thus, there is a need for more studies examining the effect of high versus low-to-moderate intensity training during treatment and especially those including muscle biopsies.

In summary, the direct effects of chemotherapy on muscle tissue in women treated for breast cancer are mostly unknown and previous studies that have investigated the direct effects of (neo-)adjuvant chemotherapy on muscle tissue and how these effects may interfere with the adaptations to strength and endurance training in women diagnosed with breast cancer have had small sample sizes. Furthermore, no previous study has compared the effects of different training intensities on muscle cells in women with breast cancer during (neo-)adjuvant chemotherapy and it is still uncertain whether high-intensity exercise is feasible in all phases of the treatment. Thus, the aim of this study is to evaluate and compare the effects of high and low-to-moderate intensity exercise on muscle cellular outcomes, muscle function, and cardiorespiratory fitness in women with breast cancer undergoing (neo-)adjuvant chemotherapy. We further aim to investigate if the effects of chemotherapy including taxanes on muscle cells are different from those of taxane-free chemotherapy.

Our hypotheses are as follows.

Both high-intensity and low-to-moderate intensity strength and endurance training during (neo-)adjuvant chemotherapy will reduce the negative treatment effects on muscle fiber CSA, mitochondrial function, cellular stress, and thus reduce the negative effects on cardiorespiratory fitness and muscle function compared to usual care. High-intensity training will be superior to low-to-moderate-intensity training in counteracting the negative treatments effects.Both high-intensity and low-to-moderate intensity strength and endurance training during (neo-)adjuvant chemotherapy will increase the muscle and blood levels of potential antitumor myokines compared to usual care.Treatment including taxane administration will have larger negative effects on muscle fiber CSA, mitochondrial function, cellular stress, and thus cardiorespiratory fitness and muscle function compared to taxane-free treatment, regardless of the training intensity.

## Methods

### Ethics Approval

This study has been approved by the Regional Committee for Medical and Health Research Ethics South-East, Norway (2015/2360).

### Study Design

This study is a 2-group randomized controlled trial (Figure 1). The participants will be randomly allocated into 1 of the 2 training groups: one group performing the combination of strength and endurance training with high intensity and the other group performing the training with low-to-moderate intensity during (neo-)adjuvant treatment for breast cancer. To measure the effect of the treatment itself, a parallel usual care group receiving no supervised training will be recruited from another pool of patients. This will be from patients living too far away from the study site to participate in training and from a usual care control group from another substudy within the Phys-Can consortium carried out at Uppsala University Hospital [31]. The usual care group will have the same inclusion and exclusion (see below) criteria as the 2 training groups in this study. Muscle biopsies, questionnaires, and blood samples will be collected from the training groups before the first chemotherapy cure (T0). The first 2-4 weeks after cure 1 will be used as a familiarization period for tests and exercises and for completing the remaining T0 tests. Testing will include measurements of physical capacity, body composition, and physical activity levels. All measurements, including muscle biopsies, questionnaires, and blood samples, will be repeated halfway into the treatment (T1) and after completion of treatment (T2). In the participants in the usual care group, measurements will be performed at T0 and T2 only. Training will start between cure 2 and cure 3 and will last throughout the treatment period, which is approximately 6 months.

**Figure 1 figure1:**
[figure not shown]
Study flowchart. HUH: Haukeland University Hospital; UUH: Uppsala University Hospital.

### Outcomes

The primary outcome for this study is muscle fiber CSA, whereas secondary outcomes include muscle function, cardiorespiratory fitness, regulators of muscle fiber size and function (including mitochondrial enzymes, heat shock proteins, protein control systems, and DNA damage), and myokines with putative antitumor effects. All outcomes are listed in Table 1.

**Table 1 table1:** Outcomes and assessments.

Outcomes and specific variables			Assessment
Muscle fiber size (muscle fiber cross-sectional area)			Cross-sections of muscle biopsies
Number of myonuclei per muscle fiber (myonuclei/fiber)			Cross-sections of muscle biopsies
Number of satellite cells per muscle fiber (satellite cell/fiber)			Cross-sections of muscle biopsies
Proteins involved in muscle hypertrophy (PI3K^a^/Akt^b^/mTOR^c^-pathway, including but not limited to mTOR^c^, P70s6k^d^, 4EBP1^e^, eIF4A^f^)			Western blot
Proteins involved in muscle protein degradation (including but not limited to FOXO^g^, ubiquitin ligase E2, LC3^h^ (I and II), p62^i^, myostatin, as well as ubiquitinated proteins)			Western blot
**Mitochondrial function**			
	CS^j^, COX4^k^, HADH^l^	Western blot	
	Mitochondrial structure	Cross-sections and whole fiber preparations of muscle biopsies	
**Cellular stress**			
	Heat shock protein (Hsp)27, Hsp60, Hsp70	Cross-sections of muscle biopsies, western blot	
	DNA damage	Comet assay	
**Physical function**			
	Muscle strength	1 repetition maximum in chest press and knee extension.	
	Muscular endurance	Repetitions until failure at 30% of 1 repetition maximum	
	Cardiorespiratory fitness	Maximal oxygen uptake	
	Lactate threshold	Blood lactate profile	
Potential antitumor myokines (including, but not limited to interleukin (IL)-6, IL-15, SPARC^m^, TWEAK^n^, IL-8, IL-10, IL-1β, IFN-γ^o^, TNF-α^p^, TNFR1^q^)			mRNA levels by real-time polymerase chain reaction analyses and protein levels by western blot and enzyme-linked immunosorbent assay
**Body composition**			
	Lean body mass, total fat mass	Dual*-*energy X-ray absorptiometry	
	BMI	Weight and height	
Physical activity (level)			SenseWear Armband
Serological outcomes (hemoglobin, creatine, cortisol, high-sensitivity C-reactive protein, total cholesterol, low-density lipoprotein cholesterol, high-density lipoprotein cholesterol, HbA^1c^)			Standard clinical measures
**Quality of life and fatigue**			
	Fatigue	Multidimensional fatigue inventory	
	Pain	Brief pain inventory	
	Health-related quality of life	European Organization for the Research and Treatment of Cancer Quality of Life Questionnaire Core 30, The European Organization for the Research and Treatment of Cancer Quality of Life for breast cancer	
Sociodemographic data (age, partnership, number and age of children living at home, education, income, work and sick leave)			Study-specific questionnaire
Lifestyle data (dietary habits, alcohol consumption, physical activity level, weight, and tobacco use)			Study-specific questionnaire
Behavioral data (motivation, self-efficacy, and barriers to training)			Study-specific questionnaire
Disease-specific information (diagnosis, type, and dose of oncological treatment, adherence to oncological treatment)			Medical records
Adverse events (adverse events occurring during exercise training sessions and during muscle biopsy sampling)			Reported by coaches/technicians

^a^PI3K: phosphoinositol-3-kinase.

^b^Akt: protein kinase B.

^c^mTOR: mechanistic target of rapamycin.

^d^P70s6k: ribosomal protein S6 kinase.

^e^4EBP1: eukaryotic translation initiation factor 4E-binding protein 1.

^f^eIF4A: eukaryotic initiation factor-4A.

^g^FOXO: forkhead box O.

^h^LC3: microtubule-associated protein 1 light chain 3.

^i^p62: ubiquitin-binding protein p62.

^j^CS: citrate synthase.

^k^COX4: cytochrome c oxidase subunit 4.

^l^HADH: 3-hydroxyacyl-CoA-dehydrogenase.

^m^SPARC: secreted protein acidic and rich in cysteine.

^n^TWEAK: TNF-related weak inducer of apoptosis.

^o^IFN-γ: interferon γ.

^p^TNF-α: tumor necrosis factor-α.

^q^TNFR1: tumor necrosis factor receptor 1.

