#### Endurance Training

During the 2-4 weeks familiarization period, participants will familiarize themselves with the use of the heart rate monitor and perceived exertion by using the Borg scale [35] for monitoring the exercise intensity and perceived exertion. All participants will perform the first session with a coach and receive training on how to use the heart rate monitor. Participants in the high-intensity training group will also be given 1-2 extra session with a coach in a gym. Thereafter, the endurance training is home-based and followed up by a coach and will be performed as previously described [34]. Briefly, the low-to-moderate intensity group perform a continuous-based exercise (running, cycling, walking uphill, or any other endurance-based activity) in bouts of at least 10 minutes at an intensity of 40%-50% of the heart rate reserve. The exercise frequency is recommended to be 2-4 times a week with the main aim to reach 150 minutes of moderate intensity per week. The high-intensity group performs high-intensity interval exercise. The sessions will consist of 2-minute intervals (running, cycling, walking uphill, or any other endurance-based activity) at an intensity of 80%-90% of the heart rate reserve (at the end of the third session) with 2 minutes of rest between intervals. During the first week, after familiarization, each session will consist of 6 intervals. Thereafter, 1 bout will be added every fourth week until 10 bouts per session are reached as the maximum, corresponding to 75 minutes of high-intensity training per week.

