#### Assessment of Physical Activity Level and Physical Training

Participants’ physical activity level will be measured using SenseWear Armband Mini (BodyMedia Inc). All participants will be instructed to wear the SenseWear Armband for 7 consecutive days. Only valid days with at least 80% wearing time will be included in the analyses. The step count cut points corresponding to moderate intensity will be 3 metabolic equivalents of task [37]. SenseWear Armband data will be analyzed with the SenseWear software (SenseWear Professional Research Software Version 8.1, BodyMedia Inc). Participants will be instructed to keep a logbook of all endurance trainings and strength trainings. In this logbook, the duration and subjective intensity measured with the Borg scale [35] of all endurance training sessions are noted. For the strength training, the load, number of repetitions, number of sets, and the perceived exertion with Omni scale are noted for each session.

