#### Background Variables

Participants will provide self-reports about age, partnership, number and age of children living at home, education, income, work, sick leave, dietary habits, alcohol consumption, physical activity level, weight, tobacco use, motivation, self-efficacy, and barriers to training by using a study-specific questionnaire. In addition, past illnesses and other medical problems are recorded. Information about the medical situations such as treatment, stage of disease, and comorbidity as well as chemotherapy treatment compliance and adverse events will be collected at all 3 assessment points (T0, T1, and T2) from medical records.

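### Exercise adverse events are limited to those during sessions and reported by coaches, yet over 90% of endurance sessions are at home, so minor or delayed events are likely to be under-recorded

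*Protocol article*

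**What the plan says.** Four places in the protocol article bear on this.

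- **Outcomes, Table 1.** The outcome is "Adverse events (adverse events occurring during exercise training sessions and during muscle biopsy sampling", and its assessment is given as "Reported by coaches/technicians".
- **Endurance Training.** "All participants will perform the first session with a coach". In addition, "Participants in the high-intensity training group will also be given 1-2 extra session with a coach in a gym". Then: "Thereafter, the endurance training is home-based and followed up by a coach". On content, "The high-intensity group performs high-intensity interval exercise", at 80%-90% of heart rate reserve. Strength training, by contrast, is described as supervised, twice a week.
- **Assessment of Physical Activity Level and Physical Training.** Participants keep a logbook of all training. For endurance sessions the listed entries are duration and Borg rating. "For the strength training, the load, number of repetitions, number of sets, and the perceived exertion with Omni scale are noted for each session". No adverse event item is listed.
- **Background Variables.** Among the items on the participant's medical situation, "chemotherapy treatment compliance and adverse events will be collected at all 3 assessment points (T0, T1, and T2) from medical records".

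**The concern.** The exercise part of the Table 1 definition is narrow in two ways. It covers only what happens during a session, so on its wording it leaves out a strain, a fall or a faint that shows itself afterwards. It also names as reporter someone who is not present at most endurance sessions. The participant, who is present, has no stated place to record an event: the logbook items listed do not include one.

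The Background Variables section gives a second source, medical records. It differs in scope and source from Table 1, and the article does not say how the two combine. A medical record would not ordinarily hold a minor event at home that led to no care.

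The use made of the count is what is at stake. The Introduction treats it as unsettled whether high-intensity exercise is feasible throughout chemotherapy, and the Discussion intends the results to shape programmes for patients. If the adverse event count comes mostly from supervised strength sessions, a low total, or similar totals in the two arms, says little about the endurance half of either programme.

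**Working it through.** The plan gives no figure to reproduce. The check is a count of sessions, followed by a comparison of sources.

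**Inputs from the article**
- Coached endurance sessions: 1 in the low-to-moderate group; 1 + 1 to 1 + 2, so 2 to 3, in the high-intensity group.
- Supervised strength sessions: 2 a week.
- Endurance frequency: 2 to 4 a week, stated for the low-to-moderate group only.
- Duration: treatment of about 6 months, with training starting between cures 2 and 3.

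**Assumptions**
- Training weeks: 18 to 26, because it is not clear how much of the 6 months precedes the start of training.
- High-intensity frequency: 2 to 4 a week. The article gives none, but at 10 bouts it gives 75 minutes a week. Counting rests, a session is 10 × 2 + 9 × 2 = 38 minutes, and two sessions make 76. Counting work only, it is 10 × 2 = 20 minutes, and 75/20 = 3.75 sessions. Both fall in or near that range.

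**Share of endurance sessions with no coach present** = 1 − coached sessions / (weeks × sessions per week)

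| Group | Lowest share | Highest share |
|---|---|---|
| High intensity | 1 − 3/(18 × 2) = 1 − 3/36 = 91.7% | 1 − 2/(26 × 4) = 1 − 2/104 = 98.1% |
| Low-to-moderate | 1 − 1/36 = 97.2% | 1 − 1/104 = 99.0% |

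**Share of all prescribed sessions**, at 22 weeks (44 strength sessions):
- With 2 endurance sessions a week there are 44 + 44 = 88 sessions. High intensity, 3 coached: (44 − 3)/88 = 47%. Low-to-moderate: (44 − 1)/88 = 49%.
- With 4 a week there are 88 + 44 = 132 sessions. High intensity, 3 coached: (88 − 3)/132 = 64%. Low-to-moderate: (88 − 1)/132 = 66%.

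So roughly half to two thirds of all sessions, and more than nine in ten endurance sessions, take place with no coach present.

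**What each stated source can capture from a home endurance session**

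| Source | Event needing care | Minor event during the session | Event appearing afterwards, no care sought |
|---|---|---|---|
| Coach report (Table 1) | If the participant tells the coach | If the participant tells the coach | Outside the definition as worded |
| Logbook (listed items) | No entry listed | No entry listed | No entry listed |
| Medical records (Background Variables) | Yes, if recorded | Unlikely | Unlikely |

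The last two columns depend on the participant volunteering the event, and the article describes no question that would prompt it.

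**The case against.** The strongest reply is that reporting is not witnessing. Table 1 does not confine the outcome to supervised sessions, and a coach can report what a participant says. Coaches follow up the home training, and every participant meets one at two strength sessions a week, so there is ample opportunity to hear of events. The medical records add the events that needed care. An article listing training-load entries does not show that the logbook holds nothing else. The way coaches ask about events may sit in the full protocol or in the earlier description of the training that the article cites.

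Much of this stands. It rules out several stronger readings that a reader might infer:

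- **That home training has no coach involvement.** The article provides for follow-up; what is missing is a coach at the session.
- **That participants are never asked.** That would be inferred from silence. The article only shows that no query and no logbook item are listed.
- **That harms are missed altogether.** Medical records can catch events that led to care.
- **That the home intervals are the riskiest part of the programme.** No section ranks risk, and the supervised strength work at 6RM and 10RM load is also intense.
- **That the arms differ materially in ascertainment.** One coached endurance session against two or three is a trivial gap, and it would tend to raise the high-intensity count, not make that arm look falsely safe.

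It is also fair that no hypothesis concerns safety, and that the article nowhere says the count will be used to declare high-intensity training safe. The two adverse event sources can be read as complementary, not contradictory.

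The reply does not reach the wording of the definition. Events after a session are outside Table 1 as it stands, and the only reporters it names are coaches and technicians. These are choices the article states, not details it leaves to another document.

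**Conclusion.** The point holds as a limited one. The stated definition and source fit supervised strength training and do not fit home endurance training. Minor or delayed events from home sessions are likely to be under-recorded, so a low or equal count would mainly reflect supervised sessions and could not support a safety comparison of the two endurance programmes.

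The coach is absent from 91.7% to 99.0% of endurance sessions across both arms, assuming 18 to 26 weeks and 2 to 4 sessions a week. The high-intensity frequency is an assumption. These percentages measure sessions without a coach present. They are not the share of events lost, which the article gives no means of estimating. The primary outcome, muscle fiber cross-sectional area, is not affected.

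**What to change.** **Definition.** Change Table 1 to cover events during or after any supervised or home session, reported by participant or coach. State how this outcome relates to the record-based events under Background Variables.

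**Collection, remaining participants.** Add an adverse event entry to the logbook for each strength and endurance session. Have the coach ask one scripted question, identical in both arms, at the existing supervised sessions about events since the last contact.

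**Reporting, all participants.**
- Tabulate events by source (coach or participant versus medical records) and by setting (supervised versus home), with logged sessions as denominators.
- Abstract record-based events over the whole T0-T2 interval in all three groups. Usual care has no T1 assessment, but its records can still be read for that period.
- State that participants enrolled before the change lacked systematic questioning about home sessions.

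**Cost.** One logbook field, one question at visits that already take place, and some extra tables. More minor events will be recorded. By June 2022, 38 + 36 = 74 of the 80 planned training participants (92.5%) were enrolled, so the new collection reaches few people and creates two ascertainment periods, which should be reported separately and not pooled. The reporting changes and the stated limitation remain possible after recruitment ends.
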